**Pinellas County Community Health Centers**

Johnnie Ruth Clarke Health Center Control

Community Health Centers Pinellas Park Intervention

Data to be collected about participating clinics:

Each clinic will be sequentially assigned a unique 2 digit ID number which will be reported in Table 1B provided to NOVA (see data dictionary).

Standard information will be collected from each clinic at the start of their participation in the project and again at the conclusion of the project. The information to be collected is described in Table 6 of the data dictionary.

D.2.1. Inclusion/Exclusion Criteria

General exclusion criteria include the following:

- Cognitively impaired
- Institutionalized
- Persons under age 18
- Previous navigation for cancer (either in PNRP or elsewhere)
- Known to be pregnant at enrollment
- Previously treated cancer (other than non-melanoma skin cancer) less than five years from diagnosis

Patients will be eligible for inclusion in the study if they receive primary medical care at one of the participating medical clinics and are noted to have a potentially cancer-related abnormality as defined below. Patients must be at least 18 years of age, but there will be no exclusion on race or income. Patients who are newly diagnosed with breast or colorectal cancer and who have not undergone any treatment will be eligible for the study.

*D2.1.1 Breast Cancer-related Abnormalities*.-- Patients having a breast-related abnormality that in the opinion of the primary physician warrants further evaluation will be eligible for inclusion. Subjects having the following breast related abnormalities will be eligible for inclusion:

- Health care provider confirmed breast mass or other abnormality suspicious for cancer prompting referral to specialist or referral for further testing
- Abnormal or incomplete mammogram (BIRADS 0, 3, 4, 5)
- Ultrasound abnormality (indeterminate or suspicious solid lesion, complex cyst, BIRADS 0,3,4,5)
- MRI abnormality (BIRADS 0,3,4,5)
- Pathologically confirmed DCIS or invasive cancer that has not been treated

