Patients having symptoms potentially related to breast cancer (abnormality noted on self-exam, breast pain, nipple discharge) will also be eligible if there are corresponding suspicious findings on clinical examination warranting referral. Patients having breast abnormalities that are fully diagnosed and treated within the primary care setting, without the need for additional evaluation, will not be eligible for inclusion in the study.

*D.2.1.2 Colorectal Cancer-related Abnormalities*.-- Patients having an abnormality potentially related to colorectal cancer, and requiring further evaluation, will be eligible for inclusion. Conditions meeting eligibility criteria include:

- Rectal bleeding in person 30 years or older with referral to specialist
- Suspicious finding on rectal exam (mass) with referral
- Abnormality on sigmoidoscopy (adenomatous/malignant polyp, mass, invasive cancer)
- Abnormal colorectal imaging (space occupying lesion by ACBE, virtual CT colonography).
- History of malignant polyp
- Positive FOBT / Guaic with referral to specialist in persons 30 years and older
- Newly diagnosed and pathologically confirmed colorectal cancer prior to treatment
- Abnormality on colonoscopy requiring additional evaluation (mass, polyp requiring excision, incomplete or unsatisfactory examination)

Patients with abnormalities that are fully diagnosed and treated in the primary care setting, without the need for additional evaluation, will not be eligible for inclusion in the study as they would have no need for navigation.

**D.3. Phase 1: To work closely with our community partners to conduct a formative evaluation of the acceptability, appeal, and appropriateness of a Patient Navigator Program.**

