**D.4.7.b Statistical Analysis and Study Power**

The statistical analyses will focus on those subjects receiving an abnormal or suspicious mammogram (BIRAD 0, 4, or 5) and those with abnormal FOBTs or abnormalities detected on sigmoidoscopy (see D.2.1). Those in the Navigator intervention groups will be compared to those in the control groups with respect to two outcomes. For patients with breast or colorectal abnormalities, the primary outcome will be time from detection of abnormality to definitive diagnosis, measured as a continuous variable. In addition, we will assess the proportion of patients who successfully complete an appropriate diagnostic evaluation. The records of each subject with such an indication for follow-up will be examined as described in D.3.3.

Study power is based on the following factors. The primary endpoint is ‘Length of time’ (LOT=time from screening to definitive diagnosis). Suppose LOT follows a normal distribution (mean=30 days, “std” = standard deviation). Then, to detect the difference in LOT between two groups (navigator versus control groups), a two-sample t-test will be used. The required minimum sample size to achieve 80% statistical power is calculated based on the t-test and illustrated in Figure 1.

For example, group sample sizes of 29 and 29 (total 58) achieve 80% power to detect a difference of 10 days between the null hypothesis that both group means are 30.0 and the alternative hypothesis that the mean of Navigator group is 20 days with estimated group standard deviations of 15.0 each and with a significance level of 0.05 using a one-sided two-sample t-test. However, to detect a difference of 5 days with the same standard deviation 15.0 between the two groups, one would need at least 112 samples for each group (total 224).

Figure 1. Required sample sizes for each group based on the expected mean of navigator group by the standard deviation. For the control group, the mean value of LOT was set up as 30.0. The standard deviations for both groups are assumed to be equal. α=0.05 (one sided: mean 1 > mean 2).

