All comparisons of the Navigator Program to the control group will be based on the ‘intent to treat principle’. That is, all patients who give consent and are registered on the study will be analyzed according to the randomized group assignment without regard to their degree of participation. Additional analyses, limited to those assigned to the Navigator Program, will explore the effects of degree of participation on the study endpoints. These analyses will incorporate participation ratings of 0 = no participation, 1 = some participation, 2 = substantial or complete participation that will be given to each patient by the Navigator assigned to that patient. Although outcome data on those patients refusing to consent in the study will not be available, we will compare those refusing to those agreeing to participate with respect to demographic variables such as age, race, gender, etc.

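### The protocol states two conflicting analysis sets for the primary comparison, a short list of abnormality types and all registered patients, and names neither as primary

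*Protocol*

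**What the plan says.** **Statistical section, opening (D.4.7.b).** For breast, the text reads "The statistical analyses will focus on those subjects receiving an abnormal or suspicious mammogram (BIRAD 0, 4, or 5". For colorectum, the same sentence names only abnormal FOBT results and sigmoidoscopy findings, and it cites D.2.1. The next sentence compares navigator and control groups. The one after it assigns the primary outcome, time from detection to definitive diagnosis, to breast and colorectal abnormalities in general, with no limit by type.

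**Eligibility (D.2.1.1 and D.2.1.2).** The section cited does not match the list. For breast it admits:
- "Abnormal or incomplete mammogram (BIRADS 0, 3, 4, 5"
- "Health care provider confirmed breast mass or other abnormality suspicious for cancer prompting referral to specialist or referral for further testing"
- "Ultrasound abnormality (indeterminate or suspicious solid lesion, complex cyst, BIRADS 0,3,4,5"
- "MRI abnormality (BIRADS 0,3,4,5"
- confirmed breast cancer, in situ or invasive, not yet treated

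For colorectum, besides FOBT and sigmoidoscopy findings, it admits "Rectal bleeding in person 30 years or older with referral to specialist", a rectal mass, abnormal colorectal imaging, a past malignant polyp, colonoscopy findings, and confirmed colorectal cancer before treatment.

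**Outcome definition (D.4.7.a).** The interval starts at the abnormality that met eligibility. Start dates are given for mammogram, ultrasound, MRI, clinical breast examination, sigmoidoscopy, colonoscopy, FOBT and imaging.

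**Intent to treat (end of D.4.7.b).** The rule covers every navigator-versus-control comparison: "all patients who give consent and are registered on the study will be analyzed according to the randomized group assignment".

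**The concern.** The opening of D.4.7.b and its intent-to-treat rule cannot both define the primary analysis. Under the first, a navigated patient who qualified only through a BIRADS 3 mammogram, a breast mass, an MRI finding or rectal bleeding falls outside the focus. Under the second, that patient is analysed. Nothing in the protocol calls the shorter list a subgroup or sensitivity set, or ranks the two.

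The choice decides which patients the primary result describes, and it may change the estimated difference. If it is left open, it could be made after results by arm are known. It also affects power, because the effective-sample table is built on everyone enrolled.

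**Working it through.** **1. The sections side by side.**

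| Finding | Eligible (D.2.1) | Specific start date (D.4.7.a) | On the D.4.7.b list |
|---|---|---|---|
| Mammogram BIRADS 0, 4, 5 | yes | yes | yes |
| Mammogram BIRADS 3 | yes | yes | no |
| Ultrasound or MRI finding | yes | yes | no |
| Clinical breast finding | yes | yes | no |
| FOBT, sigmoidoscopy | yes | yes | yes |
| Colonoscopy, colorectal imaging | yes | yes | no |
| Rectal bleeding, rectal mass, past malignant polyp | yes | general rule only | no |
| Confirmed untreated cancer | yes | general rule only | no |

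The outcome definition and the intent-to-treat rule fit the full eligibility list. The opening of D.4.7.b does not.

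**2. The plan's own figures.** Inputs from D.4.7.b: SD 15 days, one-sided alpha 0.05, power 80%.
- Normal approximation: n per group = 2 × 15² × (1.645 + 0.842)² / Δ². This gives 28 for Δ = 10 and 112 for Δ = 5.
- The exact one-sided t-test gives 28.5, so 29, and 111.97, so 112. Both match the stated 29 and 112.
- Effective N = k × 100 / (1 + 99 × ICC). For 8 clinics at ICC 0.01, 0.02 and 0.04 this is 402, 268 and 161. For 6 clinics it is 301.5, 201 and 121. All match the table.

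The table uses 100 subjects per clinic, which is everyone enrolled.

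**3. Power if only the listed findings are analysed.** Let f be the share of enrolled patients on the list. The protocol does not give f, so it is assumed here. With m = 100f:

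N_eff = k × m / (1 + (m − 1) × ICC), and power = Φ(Δ / (15 × √(4 / N_eff)) − 1.645).

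Example with 8 clinics, ICC 0.02, f = 0.6 and Δ = 5: N_eff = 480 / 2.18 = 220. The standard error is 15 × √(4/220) = 2.02, and Φ(2.47 − 1.645) is about 0.80.

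| 5-day difference | f = 1.0 | 0.8 | 0.6 | 0.4 |
|---|---|---|---|---|
| 8 clinics, ICC 0.02 | 86% | 84% | 80% | 72% |
| 6 clinics, ICC 0.02 | 76% | 73% | 69% | 61% |
| 6 clinics, ICC 0.01 | 89% | 86% | 81% | 71% |

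For a 10-day difference the loss is small. With 6 clinics, ICC 0.04 and f = 0.4, N_eff = 240 / 2.56 = 94, the standard error is 3.10, and Φ(3.23 − 1.645) is about 94%. With f = 1 it is about 98% (N_eff 121, standard error 2.73).

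**4. Effect on the estimate.** Suppose a share q of registered patients lies outside the list and gains nothing from navigation, while those on the list gain 10 days. The all-registered difference is then 10 × (1 − q): 9, 8, 7 or 6 days for q = 0.1, 0.2, 0.3 or 0.4. Both q and the zero effect are assumptions. They show only that the two sets can estimate different quantities.

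**The case against.** The best defence is that the wording is soft. To focus on some findings is not to exclude the rest, and the list may be loose shorthand for D.2.1, which it cites. The primary-outcome sentence that soon follows has no subtype limit. The intent-to-treat rule goes on to disregard degree of participation, so it may be meant to settle allocation and adherence within a set defined elsewhere. Categories also overlap: a patient with a breast mass and a BIRADS 4 mammogram is on the list anyway. A SAP, not shown, may settle the matter.

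This defence means one cannot say that patients outside the list are definitely excluded. It does not remove the conflict. A list that omits BIRADS 3 while citing a section that includes it is poor shorthand, the intent-to-treat rule speaks of all comparisons and all registered patients, and a SAP choosing either set would depart from a protocol sentence.

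A reader might infer more than the text supports:
- **Three rival populations.** Eligibility is an enrolment rule, so only two analysis sets conflict.
- **BIRADS 3 patients overturn the SD of 15.** If 5% to 20% of patients had intervals of 90 to 180 days against 30 for the rest, √(225 + p(1 − p)(D − 30)²) gives an SD of about 20 to 62, and 50 to 474 per group for 10 days. The protocol gives neither the shares nor the intervals, and 15 is itself an example value in a section whose figure varies the SD. These numbers are illustrative only.
- **The list drops patients with the greatest access barriers.** No section says barriers differ by abnormality type.
- **The 600 to 800 are the trial's total.** They are a 6-to-8-clinic scenario. D.4.3 has 12 clinics, and section E allows up to 1600 in Phase II.

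**Conclusion.** The point stands as an internal contradiction about the primary analysis set. The opening of D.4.7.b points to a short list, while D.4.7.a, the later primary-outcome sentence and the intent-to-treat rule point to all registered patients. Neither set is named primary. This is certain from the text and needs no assumption.

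The direction and size of any change in the result cannot be derived from the protocol. The power cost of the short list depends on the share of patients on it: for 5 days with 8 clinics and ICC 0.02, about 86% falls to 80% at an assumed 60%, and to 72% at 40%. For 10 days, power stays at about 94% even with 6 clinics, ICC 0.04 and a 40% share. These figures use the protocol's SD, one-sided alpha and design-effect formula, with equal arms and a normal approximation. A choice made after seeing results is a possibility that the text leaves open, not something it plans.

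**What to change.** Before outcomes by arm are seen:

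1. Replace the opening sentence of D.4.7.b with one named primary set that agrees with D.4.7.a and the intent-to-treat rule: all registered patients, analysed by their clinic's randomised assignment.
2. Adjust for, or stratify by, broad abnormality type. The detailed categories can be left to the SAP.
3. Label the set of BIRADS 0/4/5 mammogram, FOBT and sigmoidoscopy findings a sensitivity analysis.
4. State how patients whose cancer was already confirmed at enrolment enter time to diagnosis, since for them that interval had ended before navigation began. If they are left out, say openly that this is an exception to the all-registered rule, defined by status at enrolment. Wording such as unresolved abnormality would remove them without saying so.

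The cost is a few sentences in D.4.7.b. The initial abnormality and its date are already among the variables abstracted under D.3.3.1, and D.4.7.b applies the D.3.3 record review to trial subjects, so no new data are needed. If the sensitivity set is expected to carry weight, its power should be stated for the expected share of patients on the list, which the baseline abstraction could supply.

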
**D.4 Phase II: To conduct a group randomized controlled trial to evaluate the Patient Navigator Program.**

### **D.4.1 Overview of Methods**

The goal of Phase II is to test whether a Patient Navigator Program implemented in the Tampa Bay region will lead to improved timeliness of cancer care, appropriateness of cancer care, and patient satisfaction. After careful consideration of several study designs for scientific rigor, feasibility, and acceptability by our community, we have selected a group randomized design (D.4.2), with the “group” being a community health center. The intervention arm will receive the Navigator Program first, and the control arm will receive the intervention, but delayed in time to permit the evaluation of program effectiveness. Patients within groups will be recruited by Clinical Research Assistants at the time of a suspicious screening result for cancer of the breast or colorectum (D.4.3). The Patient Navigators will assist the patients who have abnormal screening findings obtain timely appointments, referrals, and financial support that may be necessary. Data will be collected from medical records regarding timing of care and adherence of care to NCCN guidelines [82, 83] with chart abstractions occurring at 12 months, and patient satisfaction occurring for a randomly chosen subsample at baseline and again at 3 months. Data will be collected to assess, among other things, the patient’s navigation through, and satisfaction with, the health care delivery system (D.4.4).

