**Navigated subjects**

The following data will be collected on navigated patients.

*Demographic Survey*

Navigated patients will provide information on demographic characteristics that are unlikely to be found in the medical record. This information will be collected in person by the navigator at the time subjects provide consent. See Demographic Survey for description of individual items.

*Measures of health literacy*

We will administer the REALM (long version) to English speaking subjects at baseline as our standard measure of health literacy. For Spanish speaking subjects, we will administer the 50 item SAHLSA instrument, also at baseline.

Measures of depression

As a potential barrier to receiving cancer related health care, participants will be screened for depression using the PRIME-MD Patient Health Questionnaire (see attached copy of instrument).

*Additional instruments*

For subjects with non cancer diagnoses, the following instruments will be administered within three months of diagnostic resolution: **Impact of Events Scale**, **Communication and Attitudinal Self-Efficacy** (CASE) general scale, **satisfaction with care survey**, **satisfaction with navigator survey**. These instruments and instructions for how they are administered are found in the NOVA Data Dictionary.

For navigated subjects with a diagnosis of cancer, the following instruments will be administered three months after initiation of treatment; Impact of Events Scale, Communication and Attitudinal Self-Efficacy (CASE) cancer scale, satisfaction with care survey, satisfaction with navigator survey.

Chart abstractions will be performed on the medical records of navigated patients approximately three months after diagnostic resolution (three months after initiation of treatment for cancer patients). Information that will be abstracted is described in the NOVA Data Dictionary

Patient demographics Table 2

Patient / Family Medical History Table 3

Charlson Comorbidity Table 4

Breast related outcomes Table 7

Colorectal related outcomes Table 9

For persons diagnosed with cancer, we will also obtain data from the treating hospital tumor registry if possible.

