**Control subjects**

The following data will be collected on control subjects.

*Demographic Survey*

Control patients will provide information on demographic characteristics that are unlikely to be found in the medical record. This information will be collected in person by the research assistant at the time subjects provide consent. See **Demographic Survey** for description of individual items.

*Measures of health literacy*

We will administer the REALM (long version) to English speaking subjects at baseline as our standard measure of health literacy. For Spanish speaking subjects, we will administer the 50 item SAHLSA instrument, also at baseline.

*Additional instruments*

For subjects with non cancer diagnoses, the following instruments will be administered within three months of diagnostic resolution: **Impact of Events Scale**, **Communication and Attitudinal Self-Efficacy** (CASE) general scale, **satisfaction with care survey**, **satisfaction with navigator survey**. These instruments and instructions for how they are administered are found in the NOVA Data Dictionary.

For control subjects with a diagnosis of cancer, the following instruments will be administered three months after initiation of treatment; Impact of Events Scale, Communication and Attitudinal Self-Efficacy (CASE) cancer scale, satisfaction with care survey, satisfaction with navigator survey.

Chart abstractions will be performed on the medical records of control patients approximately three months after diagnostic resolution (three months after initiation of treatment for cancer patients). Information that will be abstracted is described in the NOVA Data Dictionary

Patient demographics Table 2

Patient / Family Medical History Table 3

Charlson Comorbidity Table 4

Breast related outcomes Table 7

Colorectal related outcomes Table 9

For persons diagnosed with cancer, we will also obtain data from the treating hospital tumor registry if possible.

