**D.4.7.a** **Outcomes**

The primary outcome for this study is the time interval (in days) between abnormal finding suspicious for cancer and resolution. The onset of this time interval is the date of the abnormality meeting eligibility criteria *(Breast:* date that abnormal mammogram/US/MRI read by radiologist, date of abnormal clinical examination finding. *Colorectal:* date of abnormal screening [date sigmoidoscopy/colonoscopy performed, date FOBT interpreted], date that abnormal imaging test read by radiologist). If more than one abnormality meets eligibility criteria the onset of this time interval will begin with the earliest abnormality. Resolution is defined as the date that a definitive diagnosis is rendered regarding the initial abnormality. For breast, resolution may be indicated by definitive pathologic/cytologic findings (for women who undergo biopsy), definitive radiologic diagnosis, or by expert opinion (from breast surgeon). For colon, resolution will be defined by the date that pathologic interpretation of a biopsy specimen is rendered (if biopsy is performed) or by the date of diagnostic colonoscopy / radiologic imaging if no biopsy is performed. If more than one abnormality meets eligibility criteria resolution will be defined for the most clinically serious abnormality diagnosed (e.g. invasive cancer>>cancers in situ>>benign pathologic findings>>definitive radiological tests)

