Risks: A concern could be raised that a loss of privacy could occur during the focus group (Phase I) if personal information is shared with others. In Phase II, the unit of randomization is at the clinic level and thus subjects in the control group will not be receiving the patient navigator intervention. However, patients at all clinics do receive follow-up and tracking of abnormalities through existing protocols according to their established standards of care. However, in consideration that this intervention could be efficacious, we do plan to offer the Patient Navigation Program to all sites after the initial evaluation has been conducted in the first two years. Thus, all patients at all sites will be exposed to the Patient Navigation Program at some point during the project.

Minimization: Within focus groups, all participants will be told at the start of the focus groups that information shared within the group should remain within the group. Subject data will be available only to research staff involved in this project. Data will be kept in locked filing cabinets in locked research rooms. Identifying information will not be reported. With regard to patients who are randomized to the control group, they will continue to receive standard care and outreach and follow-up, which is part of the standard protocols at the community-based centers. Once evaluated under controlled conditions, the Patient Navigation Program will be offered at all sites.

Risk: Exchange of information from one institution to another (Moffitt Cancer Center and the community-based centers).

Minimization: All data exchanged electronically from one institution to another and among team members will be in aggregate form with no identifiers.

Risk Chart abstractions conducted at six months or 12 months follow-up may identify patients for whom recommended care has not yet been received.

Minimization: Research assistants will compile listings of all patients for whom chart abstractions suggest that recommended care has not been received. These listings will be forwarded to the patient’s primary physician for review. Information that will be forwarded will include patient’s name, medical record number, and a listing of the targeted health services that were recommended but not received according to information obtained in the medical record abstraction.

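### The primary t-test on days to definitive diagnosis has no value for patients who never resolve, the time-to-event analysis that could keep them is only exploratory, and chart abstraction timing conflicts

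*Protocol*

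**What the plan says.** **Outcome.** Section D.4.7.a: "The primary outcome for this study is the time interval (in days) between abnormal finding suspicious for cancer and resolution". The end of the interval is an event: "Resolution is defined as the date that a definitive diagnosis is rendered regarding the initial abnormality". Section D.4.7.b adds that "the primary outcome will be time from detection of abnormality to definitive diagnosis, measured as a continuous variable".

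**Test.** D.4.7.b names a two-sample t-test on a normally distributed time with mean 30 days. The sentence stands in the power paragraph, but no other test of the primary outcome appears. Kaplan-Meier curves and a log-rank test on the same interval are placed among exploratory secondary analyses.

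**Patients who do not resolve.** D.4.7.b also compares the arms on the proportion completing an appropriate diagnostic evaluation. E.2.2 plans lists of patients whose recommended care has not been received. Both imply that some patients will be without a diagnosis.

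**Population.** D.4.7.b, under intention to treat: "all patients who give consent and are registered on the study will be analyzed according to the randomized group assignment".

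**Abstraction timing.**
- D.4.5, navigated subjects: "Chart abstractions will be performed on the medical records of navigated patients approximately three months after diagnostic resolution".
- D.4.5, control subjects: "Chart abstractions will be performed on the medical records of control patients approximately three months after diagnostic resolution".
- D.4.1: "with chart abstractions occurring at 12 months".
- E.2.2: "Chart abstractions conducted at six months or 12 months follow-up may identify patients".

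**The concern.** A t-test needs a number for every patient, and a patient without a definitive diagnosis has none. Followed as written, the primary test can use only those who resolved. That subset is formed after randomisation, and navigation is meant to change it: D.4.4 has navigators follow up missed appointments and remove barriers to care. If navigation brings in patients who would otherwise be lost, and they resolve late, their long times enter the navigator mean while their control counterparts contribute nothing. The primary result could then understate a real benefit or show the wrong sign, and enrolling more patients would not cure it.

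The timing conflict adds to this. Unless it is settled, the length of follow-up behind the completion proportion and the censoring times is not fixed.

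**Working it through.** **1. The plan's own figures.** Inputs from D.4.7.b: SD 15 days, differences of 10 and 5 days, one-sided alpha 0.05, 80% power. The normal approximation is n per group = 2 × (1.645 + 0.842)² × (SD/difference)².
- 10 days: 2 × 6.185 × 2.25 = 27.8. The exact t-test gives 28.5, rounded up to the stated 29 (power 80.6%).
- 5 days: 2 × 6.185 × 9 = 111.3. The exact t-test gives 111.97, rounded up to the stated 112 (power 80.0%).

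Both figures reproduce, and both presuppose an observed time for every patient.

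**2. What a comparison of resolved patients would estimate.** The protocol gives no unresolved share, so these inputs are assumptions:
- uc, unresolved share in control: 10%, 20%, 30%.
- un, unresolved share with navigation: half of uc.
- T, mean days for patients resolved only because of navigation: 60 to 90.
- m, mean days in navigated patients who would resolve anyway: 30 minus the true gain. The control mean among resolved patients is 30, as in D.4.7.b.

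Navigator mean among resolved patients = [(1 − uc) × m + (uc − un) × T] / (1 − un).

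With a true 10-day gain (m = 20):
- uc 10%, T 60: (0.90 × 20 + 0.05 × 60)/0.95 = 22.1, apparent gain 7.9. T 90: 23.7, gain 6.3.
- uc 20%, T 60: (0.80 × 20 + 0.10 × 60)/0.90 = 24.4, gain 5.6. T 90: 27.8, gain 2.2.
- uc 30%, T 60: (0.70 × 20 + 0.15 × 60)/0.85 = 27.1, gain 2.9. T 90: 32.4, gain -2.4.

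Apparent gain in days (first value T = 60, second T = 90):

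| True gain | uc 10% | uc 20% | uc 30% |
|---|---|---|---|
| 10 | 7.9, 6.3 | 5.6, 2.2 | 2.9, -2.4 |
| 5 | 3.2, 1.6 | 1.1, -2.2 | -1.2, -6.5 |
| 0 | -1.6, -3.2 | -3.3, -6.7 | -5.3, -10.6 |

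In every cell navigation resolves more patients than control.

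**3. The same patients with a fixed 12-month horizon.** Restricted mean = sum of (share × mean days), with unresolved patients counted at 365 days. It is assumed that all resolutions fall before day 365 and that everyone is followed to that day. Take the worst 10-day case (uc 30%, T 90):
- Control: 0.70 × 30 + 0.30 × 365 = 130.5 days.
- Navigator: 0.70 × 20 + 0.15 × 90 + 0.15 × 365 = 82.25 days.

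The difference is 48.25 days in favour of navigation, where the resolved-only comparison shows -2.4. This quantity combines speed and completion, and the unresolved share dominates it. It shows that the sign can depend on how unresolved patients are handled. It is not a forecast of the effect.

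**4. Abstraction passages side by side.** D.4.5 counts from resolution, or from treatment start for cancer patients. D.4.1 gives 12 months and E.2.2 gives six or 12 months, neither tied to resolution. A patient who is unresolved at one year is reached under D.4.1 and E.2.2, but has no trigger under D.4.5. These cannot all be the schedule for the primary outcome.

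**The case against.** The plan does not rest on the t-test alone. D.4.7.b compares the arms on two outcomes, and the second, completion of evaluation, is where additional resolved patients would show in navigation's favour. Kaplan-Meier and log-rank on the same interval are planned as well. The t-test sentence introduces a power calculation, and detailed rules for missing outcomes often sit in an analysis plan. In the 10-day scenarios above, the apparent gain keeps its sign at unresolved shares of 10% and 20%. All of this is fair. It limits the finding to what the protocol itself fixes: a continuous primary outcome, one named test, and an exploratory label on the analysis that would suit. A separate completion comparison does not repair a biased primary one.

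Three stronger readings are tempting and go beyond the text:
- **That unresolved patients have no abstraction date.** This is so only under D.4.5. D.4.1 and E.2.2 would reach them, and D.4.7.b says the records of each subject with an indication for follow-up will be examined, with no condition of resolution. The defect is a conflict between sections.
- **That the protocol prescribes a completers-only analysis, or expressly breaks intention to treat.** No passage excludes unresolved patients. The restriction follows from using a t-test on this variable. The intention-to-treat paragraph speaks of assigned group and degree of participation, not of missing outcomes, so there is tension but no direct contradiction.
- **That the surveys must be rescheduled for the same reason.** D.4.7.b plans no between-arm survey test, and asking patients after the diagnostic episode is a defensible choice.

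**Conclusion.** The point stands. As written, the primary comparison has no place for patients without a definitive diagnosis, although the protocol expects them and intends to analyse everyone registered. The method that could include them is exploratory. This should be settled before the primary analysis, because it can change the size and possibly the sign of the main result.

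The size is hypothetical. Under unresolved shares of 10% to 30% in control, half that with navigation, and 60 to 90 days for patients resolved only through navigation, a true 10-day gain appears as 7.9 to -2.4 days. None of these shares or times comes from the protocol. The direction also depends on who is additionally resolved and how late. If few patients stay unresolved, or the shares are similar in both arms, the bias may be small.

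The abstraction conflict is a plain inconsistency and needs no assumption.

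**What to change.** **Analysis.** In D.4.7.b, make the primary analysis a time-to-event comparison of all registered patients by randomised arm, censored at a fixed 12 months from the index abnormality. Use restricted mean days to 12 months if the result should stay in days. Account for clinic clustering with a method suited to only 12 clinics; an ordinary log-rank test or an uncorrected robust variance will not do. Keep the t-test as a sensitivity analysis, labelled as restricted to resolved patients. Re-derive the sample size for the new primary analysis, since 29 and 112 per group do not carry over.

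**Data.** Reconcile D.4.1, D.4.5 and E.2.2 so that every patient in both arms, resolved or not, has an outcome abstraction at 12 months from the index date, consistent with the 12 months in D.4.1. Keep the abstraction three months after treatment start for cancer patients, so that treatment data on late diagnoses are not lost.

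**Cost.** Mostly wording, because the time-to-event methods and the 12-month abstraction are already in the protocol. The effect is no longer a simple mean difference in days unless restricted mean time is used. Some charts are abstracted later or a second time. The timing should also be checked against the NOVA Data Dictionary and the data elements set by the national steering committee (E.7).
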